**Methods:**

Participants will be randomly allocated to three clinical centers, with 30 individuals at each center, and evenly divided among the conventional treatment group, the 15-min moxibustion group, and the 30-min moxibustion group. The conventional treatment group will be administered mecobalamin and epalrestat for a duration of 4 weeks, while the moxibustion groups will receive moxubustion as an add-on therapy treatment twice a week over the same period. The duration of moxibustion differs from the 15-min group, while the procedure remains consistent across the moxibustion groups. The primary outcome is total clinical effectiveness. The second outcomes include electrophysiological examination, the Toronto Clinical Scoring System (TCSS), the Visual Analogue Scale (VAS), the Traditional Chinese Medicine Syndrome Score Scale (TCMS), and infrared thermography testing. The outcomes will be assessed during the baseline period, after the 8th treatment, and at the one-month follow-up.

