### Study design

2.1

This trial is a multi-clinical center, open method, randomized controlled trial (RCT), three-arm, parallel-group design. The study is designed to assess moxibustion as an add-on therapy to conventional treatment. This study protocol obtained approval from the Ethics Committee of the Third Hospital Affiliated with Zhejiang University of Traditional Chinese Medicine and has been registered with the Clinicaltrials registry (identification code: NCT06330233). This trial protocol is developed in accordance with the Standard Protocol Items: Recommendations for Interventional Trials (SPIRIT) guideline. The schedule of this trial is presented in Table 1, and the flow diagram of the study is shown in Figure 1.

**Table 1 tab1:** Schedule of enrolment, interventions and outcome assessments.

Study period	Baseline	Treatment phase (4 weeks)		Follow-up phase (1 month)
The time point	Week 0	Week 2	Week 4	month 1
Eligibility screening	√			
Demographic information	√			
Case data	√			
Inclusion criteria	√			
Exclusion criteria	√			
Moxibustion treatment		√	√	
Outcomes assessment				
(1) Total clinical effectiveness			√	√
(2) Electrophysiological examination	√		√	
(3) TCSS	√		√	√
(4) VAS	√		√	√
(5) TCMS	√		√	√
(6) Infrared thermography testing	√		√	
Safety evaluation		√	√	

√, required; TCSS, Toronto Clinical Scoring System; VAS, visual analog scale; TCMS, traditional Chinese medicine syndrome score scale.

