#### Moxibustion groups

2.9.2

Both moxibustion groups will receive the same conventional treatment (mecobalamin and epalrestat) as the control group, with moxibustion as an add-on therapy. In the 15-min moxibustion group, the selection of acupoints is based on traditional Chinese medicine literature (28), moxa cones will be pasted on the acupoints, and moxibustion will be applied by ignition, each time for 15 min at each acupoint, once every three days, twice a week, four consecutive weeks of treatment. To ensure standardization, the moxa cone will be kept at a distance from the skin that elicits a warm sensation without causing pain or burning, and this distance will be consistently maintained by the practitioner.

The 30-min moxibustion group will follow the same operation as the 15-min moxibustion group apart from the intervention duration.

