#### Primary outcome

2.10.1

Total clinical effective rate

Overall clinical effectiveness will be assessed at 2 time points: at week 4 and during the follow-up period (month 1). These specific time points are chosen to evaluate the immediate therapeutic effects following the completion of the 4-week treatment course and to determine the short-term sustainability of these effects 1 month after the intervention has ceased. It will be classified into the following 3 grades according to the Guidelines for Clinical Study of New Chinese Medicines:

Cure: clinical symptoms such as limb numbness, coldness and chilling pain, sensory abnormalities, muscle weakness, and muscle atrophy disappear, tendon reflexes return to normal, and the total score of TCSS is ≤ 5 points;Effective: numbness of the limbs, cold and chilling pain, sensory abnormalities, muscle weakness myasthenia, and other clinical symptoms significantly improved, tendon reflexes returned to normal, TCSS score level 2 or 1 level lower;Ineffective: clinical symptoms did not improve or worsen, tendon reflexes were not elicited, and TCSS score grade did not decrease or increase.

Total effective rate = [(number of cured cases + number of effective cases)/total number of cases] × 100%.

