#### Safety assessment

2.10.5

Detailed records of any adverse events will be maintained, including the adverse event’s onset, symptoms, duration, severity, treatment, and disappearance. The incidence rate of adverse events will be calculated by recording the number of patients with adverse reactions and dividing it by the total number of patients. In the event of adverse reactions, clinicians must assess the necessity of trial discontinuation based on patient conditions. Serious cases are to be reported to the project management office of the supporting unit and the ethics committee within 24 h. The safety of moxibustion will be assessed at each treatment session.

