## Discussion

3

As a consequence of the high prevalence of diabetes, DPN is a condition that not only places a load on individuals in terms of their mental burden and financial burden, but it also places weight on society. Most studies focus on acupuncture and electroacupuncture for the treatment of diabetic peripheral neuralgia in both clinical and basic research (16, 30–34), and there is a paucity of research on moxibustion. However, the use of moxibustion in the treatment of diabetic peripheral vascular disease is generally acknowledged in China, and impressive results have been achieved (35). The mechanism of moxibustion in treating DPN may involve the inhibition of NF-kappa B protein and mRNA expression, alongside the induction of Nrf2 protein and mRNA expression in the sciatic nerve, thereby restoring the balance between NF-kappa B and Nrf2 in rats with DPN (36). Moxibustion, although there is a scarcity of clinical studies owing to its operational instability, shows considerable effectiveness in the treatment of diabetic peripheral neuropathy. Therefore, offering a protocol for moxibustion treatment is significant.

Moxibustion, a highly regarded intervention for diabetic complications in China, enjoys popularity, particularly in the fields of rehabilitation and physiotherapy. As of now, the duration of moxibustion for addressing diabetic neuropathic pain remains uncertain and lacks a suitable and standardized protocol. Due to the operation of moxibustion’s lack of standardization, adverse events come and will bring varying degrees of impact on the health of patients such as necrotizing fasciitis (37). The phenomenon described, which pertains to accidents occurring during the moxibustion process, is relatively common. Conditions such as empyrosis, infection, and allergy may arise during surgery due to the prolonged hypoesthesia experienced by diabetic patients, particularly regarding a reduced sense of temperature (38, 39). In this case, it is essential to establish a clinical standard for moxibustion.

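### Table 1 requires no safety evaluation at the month-1 contact, so new or delayed adverse events after week 4 are captured only if patients volunteer them

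*Protocol article*

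**What the plan says.** Section 2.1, Table 1, has a row headed "Safety evaluation" with ticks under week 2 and week 4 and nothing under week 0 or month 1. The table footnote defines a tick as a required item. In the month-1 column, total clinical effectiveness, TCSS, VAS and TCMS are ticked; electrophysiology and infrared thermography are not. Section 2.10.1 explains why effectiveness is measured there: to "determine the short-term sustainability of these effects 1 month after the intervention has ceased".

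Section 2.10.5 says that records will be kept of any adverse event, covering its "onset, symptoms, duration, severity, treatment, and disappearance". It gives one time rule: "The safety of moxibustion will be assessed at each treatment session". The summary measure is a simple proportion: "The incidence rate of adverse events will be calculated by recording the number of patients with adverse reactions", divided by all patients.

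Section 2.9.2 sets the moxibustion course at "once every three days, twice a week, four consecutive weeks of treatment". The Abstract places the outcome assessments at baseline, "after the 8th treatment, and at the one-month follow-up". The control arm (section 2.9.1) takes oral drugs for 4 weeks and has no sessions.

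The Discussion gives the article's own view of the hazards. Because practice is not standardised, "adverse events come and will bring varying degrees of impact on the health of patients such as necrotizing fasciitis". It adds burns, infection and allergy, and links them to the reduced temperature sense of diabetic patients.

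**The concern.** The trial already sees every patient one month after treatment ends and requires efficacy data there, but its printed schedule does not require anyone to ask about harm. The safety record therefore depends on volunteering from about week 4 to month 1. The article itself stresses that these patients feel heat poorly, so they may not notice or connect a skin injury. A late event that nobody asks about drops out of the numerator of the incidence rate while the patient stays in the denominator, so the rate can only be too low.

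The trial is meant to guide the choice of moxibustion duration, and the Conclusion of the Abstract mentions fewer adverse effects as a possible benefit. Late skin harm in the 15-min and 30-min arms is relevant to that choice.

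A second, weaker issue is that safety checks tied to sessions exist only in the moxibustion arms. If controls are in fact evaluated only at weeks 2 and 4, adverse events in moxibustion and control would be found under different intensities of checking.

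**Working it through.** **Safety schedule against outcome schedule (Table 1)**

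| Row | Week 0 | Week 2 | Week 4 | Month 1 |
|---|---|---|---|---|
| Safety evaluation | – | tick | tick | – |
| Effectiveness | – | – | tick | tick |
| TCSS, VAS, TCMS | tick | – | tick | tick |
| Electrophysiology, thermography | tick | – | tick | – |

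Month 1 has 4 of 6 outcomes and 0 safety evaluations.

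**Number of sessions.** 2 per week × 4 weeks = 8, which agrees with the 8th treatment named in the Abstract. The session-based safety check therefore also ends at about week 4.

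**What is left uncovered**
- An event found at or before the week-4 evaluation is covered: section 2.10.5 requires its duration and disappearance to be recorded.
- A burn at session 8 may be seen at that session or at the week-4 evaluation.
- A new or delayed event after the week-4 evaluation has no scheduled prompt in any arm.

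**Effect on the incidence rate.** With 30 patients per arm (section 2.10.4), each patient whose only event is a missed late one lowers that arm's rate by 1/30 = 3.3 percentage points. The article gives no late-event rate, so the number of such patients is unknown.

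**What a month-1 check would add.** If n patients are asked and none reports a new event, the one-sided 95% upper limit for the late-event rate is 1 − 0.05^(1/n).
- Both moxibustion arms, n = 2 × 30 = 60: 1 − 0.05^(1/60) = 0.0487, or 4.9%.
- After the planned 20% dropout, n = 2 × 24 = 48: 1 − 0.05^(1/48) = 0.0605, or 6.1%.
- One arm, n = 30: 9.5%; n = 24: 11.7%.

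Without systematic asking, no such limit can be stated, because silence is not a recorded absence of events. This is general zero-event arithmetic. It shows what the check is worth and does not measure harm under the present plan.

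**Intensity of checking, conditional on reading the two safety ticks as exactly two visits.** Moxibustion patients would have 8 session checks as well as the Table 1 evaluations; controls would have 2 evaluations. The two moxibustion arms share one schedule, so their comparison with each other is balanced.

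**After the fix.** Common scheduled evaluations rise from 2 to 3 in every arm, with no added visit.

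**The case against.** **Late events can still be recorded.** Section 2.10.5 covers any adverse event with no time limit, serious cases must be reported within 24 h, and patients are in contact with the study at month 1. This stands, and it narrows the point: late events are not excluded, but nobody is required to ask about them. A reader might infer that a burn at the last session escapes the safety record altogether. The article does not support that, since the week-4 evaluation may find it and a recorded burn is followed until it resolves, including a later infection of it.

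**The hazards are mainly procedural.** The Discussion speaks chiefly of accidents while moxibustion is being given, which the session checks address. This also stands in part, but the same section names infection and necrotizing fasciitis, which need not be apparent on the day.

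**A condensed article leaves detail to the full protocol.** That is true of the method of asking and the collection window. It does not cover a schedule table that marks required items and leaves this cell empty beside four filled ones.

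**The unequal checking is not established.** A reader might infer that moxibustion patients are checked 8 times against 2 in control, and that events are up to four times as likely to be found in moxibustion. The article does not support that.
- The moxibustion row of Table 1 has the same two ticks for 8 sessions, so the safety ticks may mark the treatment phase and not two visits.
- No sentence says that controls are evaluated only twice.
- Section 2.10.5 sets out no test between arms and does not say that session findings are pooled with scheduled ones.
- The factor of four needs events lasting 3.5 days or less (28/8 against 28/2 = 14 days between checks), seen only if present at a check and never recalled. With recall, or with events lasting 14 days, the factor is 1.0. Onset and duration must be recorded, which implies that past events are meant to be captured.

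This objection succeeds against any stated size. It leaves only a conditional reporting point.

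**Conclusion.** The month-1 gap is real and is printed in the schedule: 0 safety evaluations where 4 of 6 outcomes are assessed. It is confined to new or delayed events after the week-4 evaluation, which then depend on patients volunteering them. How many would be missed cannot be derived from the article. The 4.9% and 6.1% limits assume that every patient counted is asked and that none reports a new event.

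The difference in checking between moxibustion and control holds only if the two safety ticks mean exactly two evaluations in control. Even then its size is not supported. The 15- versus 30-min comparison is unaffected by it.

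Neither part touches the primary outcome. This is a minor improvement, worth making because it costs almost nothing.

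**What to change.** - In Table 1, add a safety tick at month 1 for all three arms, using the same adverse-event questions as at weeks 2 and 4.
- In section 2.10.5, name weeks 2 and 4 and month 1 as the common evaluation times, and say that month-1 events count in the incidence rate.
- Since section 2.8 keeps outcome assessors blind to group, put the questions after the outcome assessments or have another staff member ask them.
- State whether controls are evaluated only at weeks 2 and 4. If so, any comparison of adverse events between moxibustion and control should also show the rate from the common scheduled evaluations, alongside the rate from all events, including those found at sessions.

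The cost is a few CRF items and a few minutes at an existing contact, with no new visit and no change to sample size or the primary analysis.

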#### Study monitoring and quality control

2.10.6

The research group will establish a standardized operating procedure (SOP) for the assay. One month prior to the official launch of the clinical trial, the research group will conduct a specialized training session to ensure standardized training for all participating researchers. The training will primarily concentrate on the implementation plan and associated SOPs, enabling each clinical researcher to understand the research process and specific implementation details necessary for ensuring the reliability of clinical study conclusions. All observations in the clinical study must be verified and confirmed multiple times to ensure the reliability and authenticity of the data, thereby guaranteeing that all results and conclusions in the clinical research are based on the original data. Specialized personnel will be employed to gather and quantify trial data to mitigate trial bias. A specialized data management firm will be engaged for the management of clinical data. Monthly inspections will be conducted to ensure the quality of clinical studies.

## Discussion

3

As a consequence of the high prevalence of diabetes, DPN is a condition that not only places a load on individuals in terms of their mental burden and financial burden, but it also places weight on society. Most studies focus on acupuncture and electroacupuncture for the treatment of diabetic peripheral neuralgia in both clinical and basic research (16, 30–34), and there is a paucity of research on moxibustion. However, the use of moxibustion in the treatment of diabetic peripheral vascular disease is generally acknowledged in China, and impressive results have been achieved (35). The mechanism of moxibustion in treating DPN may involve the inhibition of NF-kappa B protein and mRNA expression, alongside the induction of Nrf2 protein and mRNA expression in the sciatic nerve, thereby restoring the balance between NF-kappa B and Nrf2 in rats with DPN (36). Moxibustion, although there is a scarcity of clinical studies owing to its operational instability, shows considerable effectiveness in the treatment of diabetic peripheral neuropathy. Therefore, offering a protocol for moxibustion treatment is significant.

Moxibustion, a highly regarded intervention for diabetic complications in China, enjoys popularity, particularly in the fields of rehabilitation and physiotherapy. As of now, the duration of moxibustion for addressing diabetic neuropathic pain remains uncertain and lacks a suitable and standardized protocol. Due to the operation of moxibustion’s lack of standardization, adverse events come and will bring varying degrees of impact on the health of patients such as necrotizing fasciitis (37). The phenomenon described, which pertains to accidents occurring during the moxibustion process, is relatively common. Conditions such as empyrosis, infection, and allergy may arise during surgery due to the prolonged hypoesthesia experienced by diabetic patients, particularly regarding a reduced sense of temperature (38, 39). In this case, it is essential to establish a clinical standard for moxibustion.

The acupoints for acupuncture and moxibustion are generally quite similar (40). A meta-analysis indicates that acupuncture, when combined with conventional treatment, is effective for alleviating pain in diabetic peripheral neuropathy, especially when acupoints are situated in the limbs (16). Studies indicate that acupuncture, utilized as a complementary therapy for DPN, employs often targeted acupoints like Zusanli (ST36), Sanyinjiao (SP6), Hegu (LI4), Quchi (LI11), and Yanglingquan (GB34), among others (41, 42). ST36, SP6, LI4, and LI11 acupoints will be included in this research plan due to the evidence that diabetic peripheral neuropathy frequently impacts the small blood vessels at the extremities of the limbs and the extant clinical studies (42, 43). From the perspective of traditional Chinese medicine, ST36 and SP6 are associated with the meridians of the spleen and stomach in traditional Chinese medicine. The theory of the spleen and stomach can be used to treat patients with diabetes who have been afflicted with the disease for an extended period and have a deficiency of qi in the spleen and stomach. The hand yangming large intestine meridian is the location of 4LI4 and LI11. The yangming meridian is a meridian that is profuse in blood and qi. It has the potential to enhance the circulation of blood and qi in the meridians. The aforementioned are the proposed acupoint selections for this research strategy.

Our work demonstrates both innovation and strengths in clinical protocol. First, the acupoints were chosen based on previous research on the frequency of acupoint selection in DPN treatment (44), allowing us to make an objective choice. Second, in accordance with the traditional Chinese medical understanding of the pathogenesis of DPN, the treatment principle of warming yang and promoting blood circulation was proposed, leading to a multicenter randomized controlled trial examining the efficacy of moxibustion in treating DPN. While a systematic review by Zhou et al. (16) confirmed the benefits of acupuncture for DPN, our study adds to this by focusing specifically on moxibustion, a distinct thermal therapy whose optimal parameters are not yet established. A comparable protocol conducted to assess the efficacy and safety of moxibustion therapy for diabetic peripheral neuropathy does not address the varying durations of moxibustion treatment (21). Our protocol will examine the effectiveness and differences of moxibustion with varying durations in treating DPN and identify the optimal duration for this treatment.

Some limitations remain associated with this investigation. Firstly, unlike other studies, we cannot employ blinding due to the inherent characteristics of the moxibustion procedure. Secondly, this study uses the Visual Analogue Scale (VAS) to assess pain intensity. While widely validated for general pain, it does not specifically capture the distinct qualities of neuropathic pain. The inclusion of a dedicated neuropathic pain scale, such as the Leeds Assessment of Neuropathic Symptoms and Signs Scale (LANSS), would have provided a more nuanced assessment, and this should be considered in future research. Thirdly, the study will be conducted exclusively in Chinese populations, which may limit the generalizability of findings to other ethnic groups. Additionally, the relatively short follow-up period (1 month) may not capture long-term treatment effects or potential delayed responses to moxibustion therapy.

## Conclusion

4

This study protocol aims to determine the optimal duration of moxibustion treatment for diabetic peripheral neuropathy through a rigorous multicenter randomized controlled trial design. By comparing 15-min and 30-min moxibustion durations as add-on therapies to conventional treatment, this research will provide evidence-based guidance for clinicians and contribute to the standardization of moxibustion protocols for DPN management. The expected outcomes include improved clinical effectiveness rates, enhanced nerve function parameters, and reduced neuropathic pain, which collectively may lead to better quality of life for DPN patients and reduced healthcare burden.
